### Study population

A closed cohort was formed to identify the study population including the patients followed up at CFCs who met the following inclusion criteria according to the 2012 Registry data:patients seen at a CFC in 2012patients having two of the CF-causing mutations of the CFTR2 list published on Feb 2012patients not having received a transplant in 2012

A patient left the cohort if he or she no longer met the inclusion criteria after the annual data were updated in the Registry (2013, 2014, and 2015), i.e.: if he or she was a carrier of a mutation excluded from the CFTR2 list updated on 13/08/2015 [1]; if he or she was followed up at a CFC engaged in the PHARE-M in 2014 or 2015; if he or she changed CFC in the course of the study and in doing so, changed CFC group; if he or she received a transplant between 2013 and 2015 (data up to the transplantation were taken into account), or if the patient died between 2013 and 2015 (data up to the death were taken into account).

The cohort was divided into two groups: the “PHARE-M Group” and the “Control Group”:The “PHARE-M Group” consisted of the patients followed up at one of the 14 CFCs trained in the PHARE-M in the experimental phase (1309 patients).The “Control Group” consisted of the patients followed up at the CFCs not having benefitted from the intervention in the same period of time (2490 patients).

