At the end of the process, 1104 patients remained in each of the two paired groups. The Control Group included 20 CFCs. No paired control patients were found for 205 “PHARE-M patients”. As data are collected in the French Cystic Fibrosis Registry for all patients, exposure variables are identical in both groups. Completeness is similar: for FEV1, 20.2% and 24.5% of missing data corresponding to the children below 6 y.o., for whom this measure is not taken, and 0.6% and 3.5% for ZBMI, in the PHARE-M group and the Control group respectively. The two groups had a similar distribution by age (see Fig. 1). However, there remained a significant difference in average age at diagnosis (PHARE-M paired group: 1.9 years; control paired group: 2.5 years; *p* value: 0.0123); this could be due to the fact that newborn screening was implemented in the 1990s in Brittany, and that seven (out of the 14) CFCs in the PHARE-M Group are located in this region. Furthermore, a significant difference in FEV1% of +3.89% (*p* value = 0.0012) remained in favor of the PHARE-M patient group before the intervention (see Tables 2 and 3).

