### Analysis of the primary endpoint between the two groups

Changes over 5 years in patient health indicators are measured for 2011 (baseline), 2012, 2013, 2014, and 2015; each patient served as his or her own control. A difference in the rate of decline is expected between the two population groups, PHARE-M and control (see Fig. 2). Changes over time in FEV1% will be modeled and compared in the two groups using a mixed model for repeated data with adjustments for potential confounding variables. Measurements for a subject *i* at time *j* is given by the following model, where *ε*_*ij*_ are the normally distributed residual components with mean zero and covariance structure Σ:

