**Fig. 2 Fig2:**
[figure not shown]
Representations of the analysis of the primary endpoint

$$ {Y}_{ij}={\beta}_0^P+{\beta}_1^P{t}_{ij}+{\varepsilon}_{ij} $$ for the PHARE-M group.

$$ {Y}_{ij}={\beta}_0^C+{\beta}_1^C{t}_{ij}+{\varepsilon}_{ij} $$ for the CONTROL group$$ \mathit{\operatorname{cov}}\left({\varepsilon}_{ij},{\varepsilon}_{ik}\right)={\sigma}_{jk} $$

The covariance structure Σ is given by the *σ*_*jk*_. It allows taking into account correlation between measurements on a same subject. Correlation is assumed to be null between subjects. The choice of a covariance structure will be data driven, but we can expect that the correlation between two measurements will only depend on the time lag between them. The most realistic covariance structure should be the so-called Toeplitz covariance matrix. A special case of the Toeplitz model is the first-order autoregressive model.

The question here is to investigate whether the two slopes are parallel or not, that is to test whether $$ {\beta}_1^P $$ = $$ {\beta}_1^C $$ (*H*_0_) versus $$ {\beta}_1^P $$ ≠ $$ {\beta}_1^C $$ (*H*_1_).

Using this model, the slopes (i.e. decline in FEV1) in the two groups will be calculated and compared. Changes over time in BMI will likewise be analyzed by comparing the changes in the two groups from 2011 to 2015, taking into account the Z-score for children under 2 years of age. The average trends will be calculated and analyzed for different patient categories (such as age, sex, age at diagnosis, severity of disease expression, treatment, and certain social characteristics in the Registry). The changes over time in indicators will be presented for the “PHARE-M Group” population by CFC for crossing with the results of the qualitative study.

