### Analyses of responses and validation of the questionnaire

Responses to the items of the questionnaire are processed anonymously. Each item receives a score on a Likert scale from one to four based on the degree to which the respondent agrees or disagrees with the proposition: “Completely disagree; Disagree; Agree; Completely agree”. “No” and “Unknown” responses are assigned a score of 0. The score is reset to 100 points and can thus be totaled by theme of the questionnaire and category of respondents. An initial descriptive analysis of the responses by CFC is returned to each quality team in the month following the on-site investigation, via a web conference, in order to validate the interpretation of the scores for the different themes and identify avenues for or obstacles to continuous care quality improvement at the CFC.

A Cronbach’s alpha test will be performed on all responses collected at the centers. Since the anticipated number of respondents is around 130 people in total for the 14 teams, this test will not allow the questionnaire to be modified for use in a larger population of respondents. It mainly aims to validate the French translations of the parts of the questionnaire coming from previous studies in English and discuss the use of the parts created within this research study.

A second level of descriptive analysis will be performed by aggregating the responses (all CFCs, by professional discipline, for resource patients/parents, and for professionals) to search for potential associations between quality of care at the CFC 3 years after the PHARE-M intervention and the effectiveness of the QT and/or the engagement of parents/patients and/or contextual elements.

After the publication of the Registry report presenting the 2015 data, changes in indicators from 2011 to 2015 will be crossed with the results of the realistic part of the study, in an attempt to identify any association in relation with more favorable changes over time in patient outcomes. A “signature” set of factors associated with a maximum/minimum impact of the PHARE-M will be sought.

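### The search for drivers of PHARE-M impact uses each trained centre's own 2011–2015 change, with no control contrast or case-mix adjustment stated, and sets it against about 14–24 scores on 14 centres

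*Protocol article*

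**What the plan says.** The Abstract gives the study a second aim beside the two-group comparison: to find contextual factors that might explain why the programme performed differently among trained centres.

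The two-group comparison is controlled. Under *Analysis of the primary endpoint between the two groups*, FEV1% slopes are compared "using a mixed model for repeated data with adjustments for potential confounding variables". The same section ends with the centre-level step: "The changes over time in indicators will be presented for the “PHARE-M Group” population by CFC for crossing" with the qualitative results.

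*Analyses of responses and validation of the questionnaire* takes this up. It begins with description: "A second level of descriptive analysis will be performed by aggregating the responses". Once the 2015 Registry data are published, "changes in indicators from 2011 to 2015 will be crossed with the results of the realistic part of the study". The section closes with the aim that a signature "set of factors associated with a maximum/minimum impact of the PHARE-M will be sought".

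For this step the article states no contrast with control centres, no adjustment of the per-centre change, no number of candidate factors and no test.

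**The concern.** A trained centre's own change over four years is not an effect of the programme. The article accepts this for its primary analysis, which compares slopes with controls, but states no such comparison where it looks for factors linked to impact.

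Influences that the article itself recognises can then re-enter:

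- **Centre type and size.** The pairing section matches on both because they may confound. A display of trained centres alone brings both back.
- **Baseline status.** *Limitations identified and initial lessons* concedes that baseline differences in age at diagnosis and FEV1% could favour one group's rate of decline. The same holds between a pediatric and an adult centre.
- **Growth.** The endpoint and analysis sections tie the BMI Z-score to children under 2. Read literally, older children are followed on absolute BMI, which rises with growth whatever the centre does.

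The result would be used. *Expected results in terms of quality improvement of care* says that any factors found would guide what to work on before or alongside roll-out to the remaining centres. A factor that merely tracks age mix or noise would misdirect that effort.

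**Working it through.** The article gives no power, error rate or factor count for this step, so there is no figure to reproduce. The checks below size the problem.

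**1. Candidate scores** (counted from the qualitative *Design* section and Tables 4–10)

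| Block | Scores |
|---|---|
| Quality of CF care (chronic care model) | 6 |
| Quality-team effectiveness | 4 |
| Quality-team functioning | 4 |
| Patient/parent engagement (at least) | 1 |
| Organizational culture | 4 |
| Patient orientation, leadership | 2 |
| Multidisciplinary-team composition, quality-team composition, hospital quality support | 3 |

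The total is 24. The first two blocks (6 + 4 = 10) are treated in *Design* as results of PHARE-M. Without them, 24 − 10 = 14 mechanism and context factors remain.

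**2. Chance associations on 14 centres** (assumption: each score is read at a nominal two-sided 5%)

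- Critical |r| = t/√(12 + t²), with t the 97.5% point on 12 df: 0.532.
- Independent scores: 1 − 0.95^14 = 51%; 1 − 0.95^24 = 71%.
- 24 equally correlated scores, simulated with no true association: 61% at inter-score correlation 0.3, 48% at 0.5, 34% at 0.7.
- Expected false hits among 24: 24 × 0.05 = 1.2, whatever the correlation.
- Power for one true association: 18% at r = 0.3, 47% at r = 0.5, 85% at r = 0.7.
- If 2 of 24 factors truly had r = 0.5, expect 2 × 0.47 = 0.9 true hits and 22 × 0.05 = 1.1 false ones.
- A Bonferroni allowance for 24 scores would need |r| ≥ 0.748.

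**3. Precision of a centre slope**

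Table 2 gives an FEV1% SD of 23.96 in the paired PHARE-M group, with 1104 − 223 = 881 values, or 881/14 ≈ 63 per centre. Assumptions: SD 24, five annual values, first-order autoregressive correlation (named in the article as a special case) of 0.80–0.95 per year. The generalised least squares SD of one patient's slope is then 6.52 down to 3.65 points/year. Dividing by √n:

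| Patients | SE of centre slope (points/year) |
|---|---|
| 25 | 0.73–1.30 |
| 63 | 0.46–0.82 |
| 200 | 0.26–0.46 |

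The SE at 25 patients is √(200/25) = 2.8 times that at 200. The pairing bands run from 1–50 to 200 or more, but the sizes of the 14 centres are not given.

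**4. How much of the spread is real**

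Reliability = τ²/(τ² + SE²), with τ the true between-centre SD, which the article does not give. At SE 0.6 it is 0.15 for τ = 0.25, 0.41 for τ = 0.5 and 0.74 for τ = 1.0. The answer runs from mostly noise to mostly signal.

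**5. Growth**

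In Table 2, 182 + 209 + 213 + 169 = 773 of 1104 paired PHARE-M patients (70%) are under 20, and 182 are under 5. The under-2s, for whom the text reserves the Z-score, are therefore a small part of the young patients. Yet Table 2 reports a Z-score with only 7 of 1104 missing, so the values evidently exist for nearly everyone.

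**6. What a control contrast costs**

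A 1:1 contrast multiplies the SE by √2 ≈ 1.41, for example from 0.63 to 0.89 points/year (63 patients, autocorrelation 0.9).

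**The case against.** The strongest defence is that this is a modest exploratory step in a condensed article. The questionnaire analysis is called descriptive, the crossing is described as an attempt, the roll-out section is conditional, and the Abstract and *Scope of the study and generalization* warn about causality and volunteer centres. Much of this stands, and it rules out several stronger readings that a reader might infer:

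- **That the per-centre changes are crude.** The text does not say so. The section containing the by-centre sentence announces adjustment for confounders in the two-group model. Whether that carries over to the centre display is not stated.
- **That impact means FEV1% or BMI change alone.** *A mixed methodology* and the qualitative *Design* section also include care management and quality-team effectiveness. The concern applies to the outcome-based part of the signature.
- **That the factors found will mostly be case mix, size and chance.** This cannot be shown. It depends on the true between-centre spread, the correlation between scores and the number of real factors, none of which is given.
- **That small centres will fill both extremes.** They tend to, but the actual centre sizes are not reported.
- **That an error rate is breached.** No test or alpha is specified.

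It is also fair that a control contrast is no cure-all. Centres in the same type-and-size stratum have the same control slope subtracted, so their order does not change, and the contrast adds noise.

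The defence does not remove the core. The article says which population is shown by centre and what it is crossed with, and it names impact as the target. Its caution about few respondents concerns validation of the instruments, not the fact that this crossing has 14 units.

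**Conclusion.** The point holds as a cheap improvement. Followed as written, the step can rank trained centres partly on age mix, baseline FEV1% and growth, and present the result as variation in PHARE-M impact.

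Chance associations are likely if each score is read at a nominal 5%: about 51–71% for at least one false hit with 14–24 independent scores, falling to 48% or 34% for 24 scores correlated at 0.5 or 0.7. These figures rest on the score count and on that reading rule. The slope SEs rest on the assumed autocorrelation. The growth point rests on the text's limit of the Z-score to under-2s. The primary two-group comparison is not affected.

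**What to change.** Amend the two sections that describe the crossing, as follows.

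1. **Centre slopes.** Take FEV1% slopes from one mixed model on both groups with centre random slopes, adjusted for age × time, baseline FEV1% × time and centre type/size stratum × time, so that each trained centre is read against controls of the same type and size. State how patients without a baseline FEV1% are handled. If the 2011 value is the covariate, do not also keep it in the response.
2. **Precision.** Use the shrunken estimates, or weight raw estimates by precision, but not both. Show the intervals.
3. **BMI.** Use the Z-score for all children, not only those under 2.
4. **Factors.** Fix a short list of block scores before the 2015 outcomes are seen, and separate those treated as results of PHARE-M from those treated as mechanism or context. Report associations with confidence intervals.
5. **Wording.** Call the outcome case-mix-adjusted change rather than impact, state that the crossing has 14 units, and label the signature hypothesis-generating.

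The cost is plan text and programming on data already held. The control contrast widens centre-level intervals (up to about 1.4 times for a 1:1 contrast), does not reorder centres within a stratum and does not cure the chance problem. The 205 trained-centre patients without a paired control need a stated rule. Fewer factors will look associated.

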### Analyses of the content of the focus groups

The content of the focus groups will be exploited (coding, categorization), processed (analysis, validity), and interpreted according to the standard thematic content analysis protocol [21]. This will be done by grouping and counting within the framework developed during the pilot phase assessment.

## Discussion and conclusion

### Scope of the study and generalization

The research program aims at identifying the impact of the PHARE-M quality improvement program 3 years after the intervention at the 14 trained CFCs, situated in different organizational and cultural contexts. It uses a mixed methodology crossing the results of a quantitative analysis based on registry data and the results of a qualitative study designed in accordance with the recommendations for research on complex interventions.

The scope of the PHARE-M intervention and thus of the research concerns the management of a singular disease in a care network organized since 2002, which represents a relatively controlled scope. Therefore, the influence of contextual elements on the PHARE-M program’s impact can be analyzed independently from other confounding factors associated with different organizations for the management of various diseases or different hospital departments running diverse specialties.

Fourteen centers volunteered to engage and test the PHARE-M program; they were not randomized. Moreover, initial assessment highlighted that team motivation is a determinant of the speed of adherence to the program. This pattern of our research, focusing on an experimental phase having enlisted volunteer centers, is to be considered in interpreting the results and developing recommendations for a successful roll- out of the PHARE-M program in the national network.

Finally, the research study on the PHARE-M intervention has a study design that could be applied in the assessment of other complex interventions at healthcare settings. Hence, this research study could inform the assessment of interventions concerning the care of rare and/or chronic diseases and the instruments needed for such assessment.

### Limitations identified and initial lessons

As a result of the experimental study based on Registry data, a study population paired between two groups (intervention and control) was defined to eliminate certain confounding factors, especially factors linked to patient age distribution. Despite this pairing, significant differences remained in terms of patient age at diagnosis and primary endpoint (FEV1%) between the two groups before the intervention, in favor of the intervention group. These initial differences could have a favorable effect for the rate of decline in FEV1% in 4 years in the intervention group [22, 23]. The question is to investigate whether the slopes are parallel or not. The difference in FEV1% will be taken into account using two different intercepts in the model, one for the intervention group and one for the control group. The patients belonging to either the “PHARE-M” group or the “Control” group will be identified in the Patient Registry with respect to their group for further analysis of their health outcomes.

Moreover, on-site quality audits of the Registry data included in the calculation of the primary endpoints showed discrepancies, mainly due to the CFCs’ interpretation of the rule for selecting the values to transmit to the Registry [16]. The volume of the discrepancies identified in the data audited could be attributed to the change of the rule applied from the 2011 registry survey. This audit points out the need for a certification process to enable a larger use of this database in epidemiologic studies or for public health or pharmacovigilance purposes.

The survey conducted for the qualitative study of the multidisciplinary teams at the 14 centers should include around 130 respondents, including at most 14 patients/parents. This number of respondents might seem low for having enough statistical power in the statistical validation of the survey instruments, especially for the parts of the questionnaire developed within this research. The survey instruments could be improved within the framework of subsequent research studies aiming, for example, at comparing quality of care between centers trained in the PHARE-M and centers untrained in the program, or at making an assessment of the quality of care before/after another intervention. Therefore, this questionnaire represents an instrument that could have further uses in the network.

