### Pairing of the two “PHARE-M” and “control” groups

A preliminary analysis of the cohort formed from the 2012 Registry data showed significant differences between the two groups of patients, before the PHARE-M intervention, in terms of: 1) distribution by age, 2) distribution by age at diagnosis, and 3) distribution by FEV1% value (see Table 1).

**Table 1 Tab1:** Distribution by age, age at diagnosis and FEV1% of the 2012 study population between the two groups of the study cohort before pairing

Comparison of the two groups	PHARE-M (*N* = 1051)			Control (*N* = 1962)		
Comparison of Ages	Avg.	Med.	Max.	Avg.	Med.	Max.
Age of patients (years)	15.0	13.0	62	18.0	17.0	74
Age at diagnosis (years)	2.0	0.1	51	3.2	0.2	71
Comparison of FEV1%	Avg.	LLM	ULM	Avg.	LLM	ULM
FEV1%	83	81,55	84,45	75,48	74,33	76,64

Consequently, a 1:1 pairing of the patients from the Control Group was decided in an attempt to eliminate certain confounding factors that could be attributed to the type and size of the CFC to which the patient was assigned: each “PHARE-M patient” was associated with a “control patient” followed up at a center of the same type (pediatric, adult, or mixed) caring for a total number of patients belonging to the same interval ([1;50], [51;100], [101;150], [151;200], or [> = 200]). Reunion island CFCs were excluded from the Control Group to reduce heterogeneity in CF care. All “eligible” control patients for each patient in the PHARE-M Group were selected, and one control patient was randomly drawn from that group of eligible control patients (without replacement). The patients in the PHARE-M Group were paired in a random order.

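### Two group intercepts do not deal with the FEV1% imbalance, because the primary test compares slopes and intercepts leave slopes unchanged

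*Protocol article*

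**What the plan says.** Under *Pairing of the two “PHARE-M” and “control” groups*, the protocol article lists the differences found before pairing: "1) distribution by age, 2) distribution by age at diagnosis, and 3) distribution by FEV1% value". Each PHARE-M patient was then matched to one control on two center characteristics only, the criterion being: "followed up at a center of the same type (pediatric, adult, or mixed) caring for a total number of patients belonging to the same interval". Afterwards, "a significant difference in FEV1% of +3.89% (*p* value = 0.0012) remained in favor of the PHARE-M patient group before the intervention". Mean age at diagnosis also still differed (1.9 against 2.5 years, p = 0.0123 in the text), although Table 3 gives a Wilcoxon p of 0.1317 for the same comparison.

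Under *Analysis of the primary endpoint between the two groups*, the model has one intercept and one slope per group, and the null hypothesis is that the slopes are equal. The same section says that the mixed model will be adjusted for possible confounders. It names none there, and the equations contain none.

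Under *Limitations identified and initial lessons*, the article says of the remaining imbalance: "These initial differences could have a favorable effect for the rate of decline in FEV1% in 4 years in the intervention group". Two sentences later it gives the remedy, a separate intercept per group: "The difference in FEV1% will be taken into account using two different intercepts in the model".

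**The concern.** The threat that the article names concerns the rate of decline. The remedy that it names concerns the level. The group-specific intercepts are already in the model and have no bearing on whether patients who start higher decline more slowly. Nor does the article's point that each patient is his or her own control help, since that too removes level and not trajectory.

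At stake is the primary comparison of a non-randomized study of volunteer centers. If decline depends on starting FEV1% or on age at diagnosis, part of any slope difference would reflect who was in each group rather than the program, while the text tells the reader that the FEV1% difference has been handled.

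**Working it through.** **1. The article's own figure.** Table 2 gives FEV1% 83.00 (SD 23.96) and 79.11 (SD 25.81). With 223 and 270 missing of 1104, n = 881 and 834. The pooled SD is 24.88, so SE = 24.88 × √(1/881 + 1/834) = 1.20 and t = 3.89/1.20 = 3.24, p = 0.0012. This reproduces the stated value. The standardized difference is 3.89/24.9 = 0.16, with 24.9 = √((23.96² + 25.81²)/2). Before pairing the gap was 83 − 75.48 = 7.52 (Table 1), so 3.89/7.52 = 52% of it remained.

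**2. The other variables after pairing.** Age: 15.57 (SD 10.73) against 16.05 (SD 11.00), recomputed p = 0.30, so balanced. Age at diagnosis: 1.85 (SD 5.33, n = 1065) against 2.49 (SD 6.34, n = 1071), t-test p = 0.0117 from rounded inputs. This is consistent with the 0.0123 in the text, which therefore looks like a t-test; Table 3 reports a Wilcoxon test.

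**3. What intercepts do.** Add 3.89 to every control measurement. In the stated model the control intercept rises by 3.89; both slopes and the test of their equality are unchanged. A time-constant main effect of a covariate behaves in the same way: with complete data it leaves the slope estimates as they were. Only a covariate-by-time term can change the slope contrast.

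**4. Possible size.** Let γ be the change in annual decline per point of starting FEV1%. The documents give no γ, so the range is an assumption. False slope difference = γ × 3.89:

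| γ (points/year per point) | False slope difference (points/year) | Over 4 years (points) | Rejection, two intercepts only |
|---|---|---|---|
| 0 | 0 | 0 | 5.7% |
| 0.01 | 0.04 | 0.16 | 7.0% |
| 0.02 | 0.08 | 0.31 | 7.9% |
| 0.03 | 0.12 | 0.47 | 12.8% |
| 0.05 | 0.19 | 0.78 | 28.1% |
| −0.02 | −0.08 | −0.31 | 9.8% |

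The last column comes from 1000 simulated datasets per row with no program effect, five yearly visits, n = 881 and 834, and a two-sided 5% level. It assumes a slope SD of 1.5 points/year beyond the part explained by starting level, and a residual SD of 7. Adding the true starting level by time brought rejection to 3.6% to 6.5%. The upper end of the range is demanding: at γ = 0.05 the starting level would explain (0.05 × 24.9)² / ((0.05 × 24.9)² + 1.5²) = 1.55/3.80 = 41% of the variance in slopes between patients.

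**5. A trap in the obvious repair.** The observed 2011 value is the first response in the model. In a straight line through five yearly visits its weight in the slope is −2/10 = −0.2. With an assumed residual SD of 6, its error gives a covariance with the slope of −0.2 × 36 = −7.2. Divided by the variance 24.9² = 620, this is a coefficient of −0.0116 even when γ = 0. Across a gap of 3.89 it moves the group contrast by 0.0116 × 3.89 = +0.045 points/year in favor of PHARE-M. Simulation agrees: about +0.05, with rejection of about 7% to 8%. With 2011 removed from the responses, the false difference falls to about 0 (residuals independent between years).

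**The case against.** The strongest reply is that the methods do commit to confounder adjustment in the primary mixed model and to trends by patient category, including age at diagnosis and severity, and that the choice of covariates and interactions is normally left to an analysis plan that is not shown. This stands in part. The absence of a covariate list is no fault in an article. A reader might infer that the confounding certainly remains in the primary comparison, but the documents do not show that. What the reply does not rescue is the sentence on intercepts: it states a remedy, and that remedy cannot act on a slope. Trends by category are also not an adjusted primary contrast.

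A reader might also infer that the pairing failed because it used none of the imbalanced variables. That goes too far. Its declared target was center type and size, it brought mean ages from 15.0 and 18.0 to 15.57 and 16.05, and it roughly halved the FEV1% gap. The age-at-diagnosis imbalance is uncertain, given p = 0.1317 in Table 3 for a skewed variable.

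A reader might infer, too, that the random 1:1 draw wastes patients whom weighting would recover. That is a design trade-off. No control was found for 205 PHARE-M patients, and weighting cannot supply controls where a stratum has none.

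Finally, the sentence stands in a limitations section beside an open admission of the imbalance, and the abstract warns that causality may be hard to establish. This is fair as to tone; it does not make the remedy work.

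**Conclusion.** The concern holds in a limited form. The article names a threat to the slope and answers it with a term that cannot change the slope. The promised adjustment might remove the problem, but nothing in the article says that it acts on the slope. The primary test may therefore be biased.

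It would be tempting to say that the test is biased in favor of PHARE-M. The documents do not support that: the article says only that the differences could be favorable, and gives no relation between level and decline. Under the assumed 0.01 to 0.05 points/year per point, the false slope difference is 0.04 to 0.19 points/year. At the lower two values the false-positive rate rises only to about 7% to 8%; it reaches 28% only at the top of the range. The calculation also takes the gap from the 2012 data, because the gap in 2011, the analysis baseline, is not given.

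**What to change.** 1. Delete the statement that two intercepts take the FEV1% difference into account. Say instead that they allow for a difference in level and do not protect the slope comparison.
2. Name the confounders for the primary slope model and enter each with its interaction with time: at least age, age at diagnosis and center type.
3. Add a sensitivity analysis with starting FEV1% (or severity class) by time, in which the value used as covariate is not also a response; for example 2011 as covariate and 2012 to 2015 as outcomes. This guards against the regression to the mean shown above. If residuals are correlated between adjacent years, as the article expects, some may persist, and the text should say so.
4. Reconcile the two p-values for age at diagnosis: name the test behind each and say which one supports the statement that the groups differ.

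The cost is wording and a few model terms on variables that the Registry already holds. The primary model gains a few parameters. The sensitivity analysis loses one outcome year and the patients without a 2011 FEV1%, mainly young children.
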